## Abstract

**Background:**

Intermittent theta burst stimulation (iTBS) when applied over the left dorsolateral prefrontal cortex (DLPFC) has been shown to be equally effective and safe to treat depression compared to traditional repetitive transcranial magnetic stimulation (rTMS) paradigms. This protocol describes a funded single-centre, double-blind, randomized placebo-controlled, clinical trial to investigate the antidepressive effects of iTBS and factors associated with an antidepressive response.

**Methods:**

In this trial, outpatients (*N* = 96, aged 22–65 years) meeting the diagnostic criteria for at least moderate depression (Montgomery and Aasberg Depression Rating Scale score ≥ 20) will be enrolled prospectively and receive ten, once-a-day sessions of either active iTBS or sham iTBS to the left DLPFC, localized via a neuronavigation system. Participants may have any degree of treatment resistance. Prior to stimulation, participants will undergo a thorough safety screening and a brief diagnostic assessment, genetic analysis of brain-derived neurotropic factor, 5-HTTLPR and 5-HT1A, and cerebral MRI assessments. A selection of neuropsychological tests and questionnaires will be administered prior to stimulation and after ten stimulations. An additional follow-up will be conducted 4 weeks after the last stimulation. The first participant was enrolled on June 4, 2022. Study completion will be in December 2027. The project is approved by the Regional Ethical Committee of Medicine and Health Sciences, Northern Norway, project number 228765. The trial will be conducted according to Good Clinical Practice and published safety guidelines on rTMS treatment.

**Discussion:**

The aims of the present trial are to investigate the antidepressive effect of a 10-session iTBS protocol on moderately depressed outpatients and to explore the factors that can explain the reduction in depressive symptoms after iTBS but also a poorer response to the treatment. In separate, but related work packages, the trial will assess how clinical, cognitive, brain imaging and genetic measures at baseline relate to the variability in the antidepressive effects of iTBS.

**Trial registration:**

ClinicalTrials.gov NCT05516095. Retrospectively registered on August 25, 2022.

**Supplementary Information:**

The online version contains supplementary material available at 10.1186/s13063-023-07674-6.

## Introduction

### Background and rationale

Depression is the leading cause of years lost due to disability in the world, and current drug and psychological treatment approaches are often poorly tolerated or ineffective [1, 2]. High-frequency repetitive transcranial magnetic stimulation (HF rTMS) is now widely accepted by regulatory evidence-based medicine bodies around the world as an effective and safe therapeutic alternative for unipolar depression [3].

Intermittent theta burst stimulation (iTBS) is a modified form of HF rTMS that, when applied over the left dorsolateral prefrontal cortex (DLPFC), has documented antidepressive effects [1, 4–6]. The antidepressant mechanism of action is assumed to be increased neuroplasticity, thus facilitating normalization of neuronal circuit function [7, 8]. iTBS has shown noninferiority compared to rTMS for the treatment of depression, with reduced time consumption and discomfort for the patient [4, 6]. Previous randomized controlled trials (RCTs) have used once-a-day iTBS stimulation with 10 to 30 sessions totally, whereas studies with accelerated iTBS have employed several daily sessions [6, 9, 10]. Still, there is no scientific consensus about the optimal number of treatments or frequency of stimulation needed to achieve symptom reduction in depressed patients. However, the number of published RCT’s is still low [6, 10]. Recent data suggest substantial between patient heterogeneity in the anti-depressant response to iTBS, as is also shown for HF rTMS and other antidepressant treatments [1, 4, 11, 12]. Baseline variables associated with a favourable and relatively fast response to treatment are important to identify, as previous research suggests that early responders are those patients who eventually receive remission [13]. An improved understanding of who might benefit from iTBS or other treatment approaches for depression might be used to refine and improve the effectiveness of iTBS from a research perspective [14–16]. According to previous research, pre-treatment patient characteristics assosciated with a favourable therapeutic effect from HF rTMS are the lesser degree of treatment refractoriness and younger age [13]. Additionally, an antidepressive response observed after 10 sessions is associated with a higher probability of remission in studies using rTMS or iTBS [16]. Baseline cognitive performance could be a significant predictor for the anti-depressive response to iTBS as is previously shown for rTMS [17]. Better performance on executive cognitive tests prior to HF rTMS has been associated with a larger treatment response in major depressive disorder [15]. Improvements in performance on neuropsychological tests have been reported from previous studies applying rTMS or iTBS to the left DLPFC in depressed patients [18–21]. It has been suggested that iTBS may have more beneficial effects on cognition than rTMS in depressed patients [18, 22]. To date, few sham-controlled iTBS studies of depressed patients have included aspects of neurocognition as outcome variables [18]. Given the burden of cognitive dysfunction in MDD, the potential of cognitive improvement from iTBS alongside antidepressant efficacy is an important clinical issue [17].

Studies with rTMS and structural magnetic resonance imaging (MRI) have suggested that reduced volume of the anterior cingulate cortex (ACC) and the amygdala may be pathogenetic factors associated with depression and that smaller volumes and thickness at baseline are associated with better treatment response [18]. It is therefore likely that the same may be observed with iTBS treatment. Reduced white matter integrity measured by fractional anisotropy (FA) is also observed in depressed patients [23], and reduced FA is associated with worse cognitive performance [24]. The microstructure of white matter fibre bundles in the lateral prefrontal regions prior to stimulation may be a predictor of the antidepressive response to iTBS, as previously shown for rTMS [25, 26].

Functional MRI resting state (rs-fMRI) studies have shown that the initial strength of the neural connection between the DLPFC and the ACC could be predictive of the response to iTBS, similar to what is found in studies using rTMS [27, 28]. Furthermore, increased frontal-ACC connectivity is associated with better cognitive performance on executive tasks [29].

The brain-derived neurotrophic factor (BDNF) val66met polymorphism is associated with an antidepressant response in patients with depression [30]. Previous studies using regular rTMS have reported a trend towards better treatment effects in depressed patients with the BDNF val/val genotype [31]. Furthermore, L/L homozygotes of the serotonin transporter-linked polymorphic region (5-HTTLPR) and C/C genotype of the serotonin 1A receptor (5-HT1A) have been identified as potential predictors of the response to rTMS [14, 32]. Thus, in the present study, a genetic analysis of BDNF, 5-HTTLPR, and 5-HT1A will be performed.

### Objectives, hypotheses and trial design

The present trial is a single-centre, parallel-group, superiority, double-blind randomized controlled trial examining the effect of once-a-day iTBS compared to sham iTBS for 10 consecutive workdays in outpatients with moderate, unipolar depression. The main goals are to evaluate the effectiveness of 2 weeks of iTBS over the dorsolateral left DLPFC for the reduction of depression symptoms and to identify variables associated with the variability in the effect of iTBS on depressive symptoms. The main hypotheses of the trial are as follows:

(1) Patients receiving iTBS will display significantly larger reductions in depressive symptoms measured by the Montgomery-Aasberg Depression Rating Scale (MADRS) [33] and Becks Depression Inventory II (BDI-II) [34] compared to patients receiving sham stimulation. (2) Reduction in depressive symptoms will be significantly associated with a concomitant improvement in executive functions measured by neuropsychological tests. (3) Stronger connectivity at baseline between the DLFPC and the anterior cingulate cortices will be associated with better response to iTBS. (4) Variability in genetic measures will be significantly associated with treatment response to iTBS. (5) Variability in white matter structural measures of the brain will be significantly associated with the anti-depressive response to iTBS. The hypotheses will be investigated in separate work packages and will be reported in separate scientific articles.

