### Statistical analysis plan

Descriptive analyses of the data collected during each patient’s evaluation will be conducted up until the final evaluation. The time points for analyses are after the 5th iTBS session, 10th iTBS session and 4 weeks after the last stimulation. The follow-up 4 weeks after is used to test the stability of the reduction in depressive symptoms after iTBS and the change in symptoms after sham treatment. The effect of the intervention will be assessed as the linear change in depression scores measured on the MADRS and BDI-II.

Single means (e.g. baseline data) will be analysed with statistical methods within the framework of general linear models (GLMs) (ANOVA, linear regression, Pearson correlation, *t*-tests) if the statistical assumptions for GLMs are met. In the case of nonnormal data, nonparametric statistics will be performed. Changes in quantitative data over time will be analysed by linear mixed models (LMM), which allow for a combination of fixed and random effects. LMM estimates the parameters using all available patient data, is thus less sensitive to missing data, and has flexible modelling options for the residual covariance structure of the data [49].

Analyses of brain imaging data will be performed in separate programs according to the type of data. FreeSurfer (FS) [59] (https://surfer.nmr.mgh.harvard.edu/) will be used for the preprocessing of structural imaging data, and permutation analysis of linear models (PALM) will be used to perform statistics on structural data preprocessed in FS and in analyses where imaging data are combined with other data as covariates or factors [60]. Statistical Parametric Mapping 12 (https://www.fil.ion.ucl.ac.uk/spm/software/spm12/) will be used for the preprocessing of functional MRI data, and GIFT (https://www.nitrc.org/projects/gift) will be used for independent component analyses (ICA) and statistical analyses of rs- fMRI.

Missing data will be described for each group at all time points of measurement, and imbalances will be evaluated. Missing data will not be imputed in the analyses. Any patient who drops out will be described according to group, exit date, exit reason, characteristics at inclusion and last data collected.

An alpha value of 0.05 will be used for all analyses, and Bonferroni corrections will be applied when appropriate for controlling the type 1 error rate.

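### Hypothesis 4 names no locus, contrast or direction, so a genetic result opposite to its own rationale would satisfy it; Holm could replace Bonferroni at no cost in error control

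*Protocol article*

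**What the plan says.** The protocol article (Objectives, hypotheses and trial design) lists five main hypotheses. The fourth reads "Variability in genetic measures will be significantly associated with treatment response to iTBS". The third, in the same list, concerns another baseline predictor and does state a direction: "Stronger connectivity at baseline between the DLFPC and the anterior cingulate cortices will be associated with better response to iTBS".

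Background and rationale gives the basis for the genetic hypothesis. For BDNF, earlier studies of regular rTMS "reported a trend towards better treatment effects in depressed patients with the BDNF val/val genotype". L/L at 5-HTTLPR and C/C at 5-HT1A "have been identified as potential predictors of the response to rTMS". The paragraph then concludes that "in the present study, a genetic analysis of BDNF, 5-HTTLPR, and 5-HT1A will be performed".

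On error control, the Statistical analysis plan section says: "An alpha value of 0.05 will be used for all analyses, and Bonferroni corrections will be applied when appropriate". It does not say whether the three loci are corrected together. Each hypothesis goes to its own work package and article.

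**The concern.** The rationale consists of three genotype-specific expectations, but the hypothesis drawn from it keeps none of them. If patients without val/val, without L/L or without C/C responded better, and the difference were significant, hypothesis 4 would be met as written even though its rationale would be contradicted. Identifying variables associated with response is one of the trial's two stated main goals, so a reader of the genetic article should be able to tell confirmation from contradiction. A direction that is first stated after the genetic data have been analysed carries little weight.

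The choice of correction matters as well. If the article makes a separate claim for each locus, or for each test in any other corrected family, Bonferroni gives up power that Holm keeps at the same family-wise error rate.

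**Working it through.** **Inputs.** Three loci (Background and rationale). Alpha 0.05, with Bonferroni where judged appropriate (Statistical analysis plan). 86 evaluable patients, 43 per group (Sample size calculation); the recruitment figure follows as 86/0.9 = 95.6, rounded up to 96. The plan gives no error rate or power for the genetic tests, so there is no figure of its own to reproduce on this point. Assumptions made here: one two-sided test per locus, and independent loci.

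**1. Chance that at least one locus is significant when none is associated.**
- Uncorrected: 1 − 0.95³ = 1 − 0.8574 = 14.3%.
- Bonferroni over three (0.05/3 = 0.0167 each): 1 − 0.98333³ = 4.9%.

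**2. Chance that at least one locus is significant in the direction opposite to the named genotype.** Half of each two-sided alpha lies on that side.
- Uncorrected: 1 − 0.975³ = 1 − 0.9269 = 7.3%.
- Bonferroni over three (0.0167/2 = 0.00833 each): 1 − 0.99167³ = 2.5%.

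These events are contained in those of step 1. Correction makes the wrong-direction route rarer, but does not change what the hypothesis counts as support.

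**3. Holm against Bonferroni.** With k tests, Bonferroni compares every p-value with 0.05/k. Holm compares the smallest with 0.05/k, the next with 0.05/(k − 1), and so on, stopping at the first failure. Every Bonferroni rejection is therefore also a Holm rejection. The first step is identical, so the chance of at least one rejection is identical too.

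Size of the gain, by simulation with normal test statistics. Assumed: standardised difference d = 0.6 and two groups of 43, so the mean of each statistic is 0.6 × √(43/2) = 2.78. For the loci this means that the named genotype splits the 86 patients evenly, which the article does not tell us.

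| Family | Real effects | Average power, Holm | Average power, Bonferroni | At least one rejection (both) |
|---|---|---|---|---|
| 3 independent tests | 3 of 3 | 74% | 65% | 96% |
| 3 independent tests | 1 of 3 | 65% | 65% | 66% |
| 4 tests, correlation 0.5 | 4 of 4 | 70% | 61% | 88% |
| 4 tests, correlation 0.5 | 1 of 4 | 61% | 61% | 63% |

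The four-test rows illustrate a family such as correlated cognitive measures compared between arms; they are not genotype contrasts. With no real effect among three independent tests, both methods reject at least once in 4.9% of runs.

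**The case against.** **The evidence for a direction is thin.** Only the BDNF sentence says that the named genotype does better, and it reports no more than "a trend towards better treatment effects in depressed patients with the BDNF val/val genotype". For L/L and C/C the text speaks of predictors of response without saying better. All of this comes from rTMS, not iTBS. A reader might infer that the background states a favourable genotype at every locus; at two of the three this is only the natural reading. The point stands in part. Two-sided testing is defensible on such evidence. It does not require the hypothesis to count both directions as support, and hypothesis 3 shows that the authors state a direction where they hold an expectation.

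**The plan provides a correction.** A reader might infer a planned false-positive rate well above 5%, or that hypothesis 4 can hardly fail. Neither is supported. The 14.3% is the uncorrected case, Bonferroni over the three loci gives 4.9%, and null results at all three loci would fail the hypothesis.

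**Coding and the definition of the family belong to an analysis plan that is not shown.** This is right, and their absence from an article is no finding. If additive, dominant and recessive codings were all open and uncorrected, simulations under assumed allele frequencies put the rate at about 21% to 29%. The documents give no frequencies and do not say that several codings will be tried, so nothing here rests on that. What the article does fix is the wording of the hypothesis and the name of the correction.

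**Bonferroni is valid, and Holm does not help with an any-locus claim.** Both statements are correct. Holm is an improvement, not the repair of an error, and it helps only when loci or tests are claimed one by one and more than one effect is real.

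**Conclusion.** The point holds as a minor one. As worded, hypothesis 4 is met by a significant association at any of three loci in either direction, including one that contradicts the background. Under independence and one test per locus, the wrong-direction route has probability 7.3% uncorrected and 2.5% with Bonferroni over three when no locus is associated. The total false-positive rate is 14.3% and 4.9% respectively. Correction controls the rate but leaves the wording open.

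Replacing Bonferroni by Holm keeps family-wise error at 0.05 and never lowers the power of an individual test. The average gain is about 9 percentage points if all effects are real at d = 0.6, and almost nothing if only one is. The effect size and the even genotype split are assumptions.

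The consequence is confined to a secondary work package. A reader might extend the concern to the trial's main result, but the primary MADRS comparison does not depend on hypothesis 4.

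**What to change.** **Objectives, hypotheses and trial design.** Restate hypothesis 4 as three contrasts, each expecting better response with the named genotype than with all other genotypes at that locus: val/val (BDNF), L/L (5-HTTLPR) and C/C (5-HT1A). Treat the three as one family. Two-sided tests can stay, with the statement that a significant result in the opposite direction does not support the hypothesis. Any other genotype coding is exploratory. If the authors hold no directional expectation for L/L or C/C, they should say so there.

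**Statistical analysis plan.** Replace Bonferroni by Holm for every family that is corrected.

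**Cost.** Two short edits, with no extra patients or data, best made before the genetic data are analysed. A different inheritance pattern could then be reported only as exploratory. Simultaneous confidence intervals are less simple under Holm than under Bonferroni.

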## Methods

We used the SPIRIT reporting guidelines [35], see the attached SPIRIT checklist.

### Recruitment and study setting

Participants will be recruited prospectively, and the study will be performed at laboratories at the UIT, the Artic University of Norway, and the University Hospital of North Norway-Health Trust (UNN-HF).

Information about the research project is distributed at the outpatient clinic at the UNN-HF and to general practitioners in the city of Tromsø, Norway. Participants must contact the study themselves.

### Eligibility criteria

Participants must be between 22 and 65 years of age at inclusion, be fluent in the Norwegian language, and meet the diagnostic criteria of at least moderate depression according to the MADRS. A MADRS score ≥ 20 usually indicates moderate depression [33]. Patients must provide informed written consent, be able to follow the treatment schedule, and have a satisfactory safety screening for iTBS and MRI.

Patients will be excluded from the study if the clinical assessments performed at baseline indicate that the current depressive episode is in the mild range or, on the contrary, that the current episode fulfils the criteria for severe depressive episode requiring inpatient treatment, acute suicide risk is present or if the current depressive episode is clearly triggered by grief or a recent major stressful life event. The clinical assessment indicates the likelihood of bipolar disorder, dysthymic disorder, psychotic symptoms, alcohol or substance abuse/addiction in the last 6 months, current eating disorders, obsessive–compulsive disorders or posttraumatic stress disorder. Further exclusion criteria due to safety issues are a medical history of seizure, neurological or neurosurgical pathologies, cardiac or systemic disease, metallic prosthetic material or foreign objects (pacemakers, prosthetic eye equipment, etc.) and being pregnant or breast-feeding [36, 37]. Additionally, if patients have a previously diagnosed developmental disorder (learning disabilities, AD/HD or autism spectrum disorder) and a borderline personality disorder or is an active user of illegal drugs, they are also excluded.

No treatments are prohibited during the trial, but drug therapy must have been stable for the last 3 weeks prior to the first treatment day with iTBS and must be kept stable throughout the study until 4 weeks after the last day of iTBS treatment. All concurrent treatments will be recorded.

### Schedule of enrolment, interventions and assessments

Prior to enrolment, detailed information about the study is provided, and a medical doctor does an eligibility screening (safety check, inclusion/exclusion criteria) by telephone, and the consent form is sent by mail. If an eligible patient still wishes to participate after this step, the written informed consent form must be handed in at the study site prior to the baseline assessments. At the study site, a certified clinician (medical doctor or specialist in clinical psychology) performs a relatively brief clinical assessment. The participant thereafter fills out questionnaires and completes a cognitive assessment. Cerebral MRI and blood sample collection are conducted at the hospital laboratories. Preferably within 3 days and not more than a week after the baseline assessments, patients are allocated to receive either sham or active iTBS once a day for 10 consecutive workdays. A clinician blinded to the stimulation parameters will evaluate the level of depression after the 5th session of active iTBS/sham stimulation, after the 10th session of iTBS/sham stimulation and 4 weeks after the 10th stimulation. Cognitive assessment and questionnaires from the baseline assessment will be repeated after 10 stimulations. A final telephone assessment of depression level is done at close-out, 4 weeks after the last stimulation day. At close-out, group allocation is disclosed to the patient. If the patient still fulfils the criteria for moderate depression at this point, 10 once-a-day sessions with open-label iTBS are offered. Table 1 shows the *Schedule of enrolment, interventions and assessments.*

**Table 1 Tab1:** Schedule of enrolment, interventions and assessments

Time point	Study period				
	Enrolment		Post allocation		Close-out
	Pre-enrolment	Baseline	After 5 stimulations with iTBS or sham	After 10 stimulations with iTBS or sham	4-week follow-up post-last stimulation day
Screening for eligibility and safety^a^	X	X			
Randomization	X				
**Allocation**		X			
Written informed consent		X			
